## Hypothesis

2

The sLiFE group intervention is more effective than usual health advice for the prevention of falls in older adults people living at home.

## Methods

3

### Design

3.1

Multicentre randomised clinical trial with two parallel arms, designed according to the CONSORT statement. This protocol has followed the SPIRIT guidelines for randomised trials. It was registered with ClinicalTrial.gov in June 2023 under the identifier NCT05912088.

### Sample/participants

3.2

The study population will comprise subjects aged over 65 years who be in agreement to take part in the study and are being treated in the primary care setting of the Health Area of “X.” This study was reviewed and approved by the Salamanca Drug Research Ethics Committee in July 2022 under registration number PI 2022 071126. Before the study onset, all participants will be informed of the study objectives and will sign an informed consent form. Throughout the study the standards established in the Declaration of Helsinki will be followed. All those meeting the inclusion criteria in the health centres will be invited to participate.

#### Inclusion criteria

3.2.1

older adults older 65 years, living at home and speaking and reading Spanish.

#### Exclusion criteria

3.2.2

Heart failure (NYHA class III-IV); previous stroke (<6 months); Parkinson’s disease diagnosis; in active cancer treatment (last 6 months); chronic obstructive pulmonary disease (GOLD class III-IV); lower extremity fragile fracture; lower extremity amputation, treatment for depression less than six months ago, resting systolic pressure blood pressure > 160 or diastolic pressure > 100 uncontrolled; unavailable for the intervention, having more than two months travel or transfers planned in the first six months of the study; cognitive impairment moderate–severe (Mini Mental Cognitive Assessment <23); simultaneously participation in another clinical intervention trial.

### Sample size

3.3

The main variable of the study was used to estimate the sample size, the annual incidence rate of falls in this population. An alpha risk of 0.05 and a beta risk of 0.2 (Power for Chi square 80% and t-test 94%), effect size estimated 0.30 (Cohen D) and 0.01 (V de Cramer) in a two-sided contrast has been accepted, 325 participants in the intervention group and 325 in the control are needed to find differences of ten percentage points as statistically significant between the control group, expected to be 30% [the estimate of falls in people older than 65 years of age (3, 5, 6)] and the intervention group, expected to be 20%. A give up rate of 10% during follow-up has been estimated.

This data has been calculated following the formula for qualitative variables published by Argimon Pallàs et al. (25).

$N=\frac{Za.Ö\;2.p.\left(1-p\right)+ZbÖ\;p1.\left(1-p1\right)+p2.\left(1-p2\right)2}{\left(p1-p2\right)2}$

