#### Stage four

3.6.4

Follow-up evaluation at six months.

Spirit figure has been added as Supplementary material.

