### Procedures

3.8

Six months after the initial control group assessment and six months after the intervention group sessions have finished, subjects of both groups will be assessed with the same tests that were carried out in the initial assessment. After random assignment, follow-up assessments will be performed by the blind group assignment assessors. The database used in this study will only display information unrelated to the intervention when they are logged in to ensure the blinding of assessors. Should a participant wish to withdraw from the study, they will continue to be eligible to complete the follow-up measurements with their consent. Researchers will record the reasons and date of withdrawal, but data recorded before withdrawal will be used unless the participant decide to use their right to have all data deleted.

Study data will be collected and managed using REDCap electronic data capture tools, hosted at the University of “X.” REDCap is a secure, web-based software platform designed to support data capture for research studies.

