### Statistical analysis

3.9

The study population baseline characteristics will be expressed as means ± standard deviation (SD) for quantitative variables and in frequency distributions for categorical variables. Student’s t-test, chi-square, and Fisher’s exact tests will be applied to find differences in baseline characteristics between intervention and control groups. All analyses of the variables obtained from the questionnaires will be analyzed using the reliability and validity criteria proposed by their authors.

The main analyses will be performed on the intention-to-treat principle, so all randomised subjects will be included in the data analysis set for which the initial assessment was performed. Participants who withdraw or drop out will be asked to be included in follow-up measurements; those lost to follow up will be considered in the full set of analyses as missing data. Detailed modelling of variations between participants and groups will be done in terms of factors such as dose, acceptability, and contextual factors. Using the Chi-square test, we will compare the proportions of subjects who have had a fall in both groups. The comparison of all outcomes between baseline, six and twelve months will be carried out using the two-way repeated measures ANOVA. Logistic regression analysis will be conducted to determine the influence of the different risk factors on falls. Statistics analysed will be performed with SPSS V.25.0 statistical package (SPSS Inc., Chicago, Illinois, United States). *p* values for cut-off values for significance were established at <0.05 (two-tailed). Results were interpreted according *[Cohen]*, who considers small size if Cohen D are between 0.2 ≤ and < 0.5; average effect size if differences are between 0.5 ≤ and < 0.8 and very high effect size if differences are ≥0.8 (38).

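### The sample size uses a one-year fall risk, but the follow-up sections describe six months counted from different starting points in the two arms; the stated 80% power holds only with a common 12-month fall window

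*Protocol article*

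**What the plan says.** - **Basis of the sample size (section 3.3).** "The main variable of the study was used to estimate the sample size, the annual incidence rate of falls in this population". The assumptions are a 10-point difference, with controls at 30% and intervention at 20%, two-sided alpha 0.05, 80% power for the chi-square test and 10% loss. The section concludes that "325 participants in the intervention group and 325 in the control are needed to find differences of ten percentage points as statistically significant". The Introduction confirms that 30% is the share of people over 65 with at least one fall in a year.
- **Follow-up (section 3.6.4).** "Follow-up evaluation at six months". No later evaluation is listed.
- **Follow-up (section 3.8).** One repeat assessment, timed differently by arm: "Six months after the initial control group assessment and six months after the intervention group sessions have finished". Section 3.6.3 gives the sessions a length of twelve weeks.
- **Analysis (section 3.9).** "The comparison of all outcomes between baseline, six and twelve months will be carried out" by repeated measures ANOVA. This is the only mention of a twelve-month time point. The chi-square comparison of the proportions who fell, in the same section, has no window.
- **Collection of falls (section 3.7.8).** A daily log is sent in every month, with telephone contact after a fall. The section does not say for how long.

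**The concern.** A risk of falling has meaning only over a stated period, and the proportion who fall at least once grows with that period. The trial is sized on one year. The sections that describe what happens to participants stop at six months, and the one section that names twelve months does not attach it to the test on fallers. These statements do not fit together.

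Two things are at stake. First, if falls are counted for less than a year, both risks and the difference between them shrink, and 325 per arm no longer gives 80% power. Second, the clock in section 3.8 gives the intervention arm a longer period from baseline than the control arm. If falls were counted up to those assessments, the intervention arm would have more time in which to fall, and the comparison would be biased against the programme whatever the sample size.

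**Working it through.** **Inputs.** From section 3.3: p1 = 0.30 and p2 = 0.20 (annual), two-sided alpha 0.05 (z = 1.960), power 80% (z = 0.8416), 325 per arm, 10% loss. Evaluable per arm: 325 × 0.9 = 292.5, taken as 292. From section 3.6.3: 12 weeks of sessions.

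**Step 1: reproduce the plan.** With p̄ = 0.25,

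n = [1.960·√(2·p̄(1−p̄)) + 0.8416·√(p1(1−p1) + p2(1−p2))]² / (p1−p2)²
= [1.960 × 0.6124 + 0.8416 × 0.6083]² / 0.01 = 293.1, so 294 per arm.

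Allowing for 10% loss gives 294/0.9 = 327 or 294 × 1.1 = 324. Both agree with 325. The arithmetic in section 3.3 is sound.

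Power = Φ{[d·√n − 1.960·√(2p̄(1−p̄))] / √(p1(1−p1) + p2(1−p2))}. At n = 292: (1.7088 − 1.2002)/0.6083 = 0.836, so power is 79.8%. With no loss (n = 325) it is 83.9%.

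**Step 2: a common six-month window.** The document gives no six-month risks, so they must be assumed. Three conversions:

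- *Simple halving:* 15% vs 10%.
- *Constant hazard:* 1 − 0.70^0.5 = 16.3% and 1 − 0.80^0.5 = 10.6%.
- *Geometric fall counts:* the mean annual count is 0.30/0.70 = 0.4286 and 0.20/0.80 = 0.25. Halved, these are 0.2143 and 0.125, so the risks are 0.2143/1.2143 = 17.6% and 0.125/1.125 = 11.1%.

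| Assumption | Six-month risks | Power, 292 per arm | Power, 325 per arm | Evaluable per arm for 80% |
|---|---|---|---|---|
| Halving | 15% vs 10% | 45% | 49% | 686 |
| Constant hazard | 16.3% vs 10.6% | 53% | 58% | 547 |
| Geometric counts | 17.6% vs 11.1% | 61% | 66% | 452 |

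The geometric model implies that 30% of control fallers fall again within the year, which matches the Introduction, but only 20% of intervention fallers. Holding 30% recurrence in both arms with a negative binomial gives 17.6% vs 11.8% and 51% power at 292 per arm, inside the range shown.

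**Step 3: the clock in section 3.8.** Twelve weeks is 84/30.44 = 2.76 months. If sessions start at the initial assessment (an assumption; any wait for a group to form would add to this), the intervention assessment falls at 6 + 2.76 = about 8.8 months, against 6 months for controls. Under a constant hazard, counting falls to each arm's own assessment:

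- Planned effect present: control 1 − 0.70^(6/12) = 16.3%; intervention 1 − 0.80^(8.76/12) = 15.0%. The difference is 1.3 points, and power is 6.3% at 292 per arm and 6.6% at 325.
- No effect at all: 16.3% vs 1 − 0.70^(8.76/12) = 22.9%. An inert programme would look harmful.

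**Step 4: other common windows.** Under a constant hazard at 292 per arm, power is 68% at 8.8 months and 79.8% at 12 months. Of the windows considered, only the full year gives the stated figure.

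**The case against.** The strongest reply is that an assessment visit is not a fall-observation window. Section 3.8 concerns repeating the baseline tests. Falls come from a separate monthly log with no six-month end stated, section 3.3 names an annual incidence as the main variable, and section 3.9 includes twelve months. Read together, these are consistent with counting falls for a year in both arms, and then about 80% power is delivered.

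This stands. A reader might infer that the trial is underpowered, or that the fall test will be run at six months. The document does not support that, because no section says so. A reader might also infer that the primary time point is open to choice after the data are seen. That cannot be shown either, because the schedule figure is in supplementary material and an analysis plan may exist, and either could name the window.

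What the reply does not remove is the conflict on the page. Section 3.6.4 ends at six months, section 3.8 describes no twelve-month assessment, and section 3.9 compares outcomes at twelve months. Nor is this a matter of an article abbreviating its source, since the statements that remain disagree. A later analysis plan could choose a window, but it could not supply log months that were never collected.

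**Conclusion.** This is an internal inconsistency with a conditional loss of power. The sample-size calculation is correct for annual risks, and its 80% is delivered only if falls are counted over 12 months from a common start in both arms.

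If a common six-month window is used instead, power at 292 evaluable per arm is about 45% to 61%. That range depends on how falls are assumed to spread over the year and among people, which the document does not give. If falls are counted to the arm-specific assessments in section 3.8, exposure is unequal and power for the planned effect is about 6% to 7%, assuming a constant hazard and sessions that start at baseline. In that case the bias matters more than the power.

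The point should be settled before follow-up is under way, because falls are a primary outcome and the sole basis for the sample size.

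**What to change.** State in section 3.9 one fall-observation window for the chi-square comparison, counted from randomisation and identical in both arms, and bring sections 3.3, 3.6.4 and 3.8 into line with it. There are two ways to do this:

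1. **Twelve months.** This matches the annual risks and keeps 325 per arm and the stated power. The cost is more months of log collection and of telephone follow-up after falls. Whether the other outcomes also need a twelve-month visit is a separate matter: section 3.9 compares all outcomes then, section 3.8 schedules no such visit, and adding one would have its own cost.
2. **Six months.** Restate the expected six-month risks and the resulting power (about 45% to 61% at 292 per arm) in section 3.3, naming the assumption used. The cost is a less favourable stated power or, if 80% is to be kept, 452 to 686 evaluable per arm before allowing for loss.

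Under either option, say explicitly that the arm-specific timing in section 3.8 does not define the period over which falls are counted.

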### Participant assessment

3.4

An external researcher will receive the participants and carry out the initial evaluation. The interview will be completed with information from the participants’ primary care medical history and the records of the University Hospital of “X.” The visit will take around 50–60 min and includes the collection of sociodemographic data, lifestyle, physical activity, cognitive status, adherence to exercise, quality of life and fear of falling. Participants will be fitted with a digital pedometer to record their physical activity for eight days. After the initial assessment, participants will be randomized to the intervention or control group.

### Randomisation

3.5

Once the inclusion criteria have been assessed, participants will sign informed consent and will then be randomised into the intervention/control group (Figure 1). An independent investigator, blinded until groups have been assigned will be in charge of generate the allocation sequence generated in a 1:1 ratio using the Epidat 4.2 software package. Considering the nature of the study, participants cannot be blinded to the intervention.

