**Methods:**

The study will comprise 650 participants with more than 65 years who live at home, observing established inclusion and exclusion criteria. Participants will be randomly assigned in two groups: group intervention (*n* = 325) and standard health advice (*n* = 325). The intervention group will follow the balance and strength activities described in the LiFE program manual. The group intervention will be carried out in groups of 12–14 and will consist of seven one-hour sessions over 12 weeks in health centres. Incidence of falls and quality of life will be assessed as primary outcome variables. Fear of falling and exercise adherence will be analysed as secondary outcome variables.

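### Individual allocation directly after consent is not tied to the assembly of the 12–14-person groups, so intervention participants may wait at risk before session 1

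*Protocol article*

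**What the plan says.** All references are to the protocol article.

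- **Design (3.1):** "Multicentre randomised clinical trial with two parallel arms".
- **Order of steps (3.4 and 3.5):** the initial assessment comes before allocation, and after eligibility is checked "participants will sign informed consent and will then be randomised into the intervention/control group".
- **Allocation list (3.5):** "allocation sequence generated in a 1:1 ratio using the Epidat 4.2 software package". Neither batches nor the health centre are mentioned.
- **Delivery (Abstract, 3.6.2, Table 1):** "The group intervention will be carried out in groups of 12–14". Five on-site sessions fall in weeks 1, 2, 3, 4 and 6, and telephone contacts in weeks 8 and 12. Each of the first four sessions teaches different activities.
- **Falls (3.7.8):** a daily log returned each month, with no start date given.
- **Follow-up visit (3.8):** six months after the initial assessment in the control arm, but six months after the sessions end in the intervention arm.
- **Main fall comparison (3.9):** a chi-square test on the proportion who fall, by intention to treat. The section also names six- and twelve-month time points for comparing outcomes.

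**The concern.** Allocation is described person by person, but the programme is delivered to a group that moves through a set sequence of sessions. Someone who joins at week 3 has missed the earlier activities, so a group would normally be assembled before session 1. Read literally, the text places allocation before that assembly. A person allocated early may then wait for session 1, while a control participant has nothing to wait for.

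Two things are at stake. First, if falls are counted from randomisation, falls during the wait belong to the intervention arm although the programme has not begun, and the contrast shrinks. Second, because 3.8 times the control visit from the initial assessment and the intervention visit from the end of the sessions, any wait adds time at risk to the intervention arm alone.

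**Working it through.** **Inputs from section 3.3.** "An alpha risk of 0.05 and a beta risk of 0.2", "in a two-sided contrast has been accepted"; "Power for Chi square 80% and t-test 94" (per cent); "between the control group, expected to be 30" (per cent), against 20% in the intervention arm, both annual; 325 per arm; 10% dropout.

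**Step 1: reproduce the stated sample size.** With pooled variance, p̄ = 0.25 and no continuity correction:

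n = [1.96·√(2·0.25·0.75) + 0.842·√(0.30·0.70 + 0.20·0.80)]² / 0.10² ≈ 293.2, so 294 per arm.

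Allowing for 10% dropout gives 294/0.9 = 327, or 294 × 1.1 = 324. Both agree with 325. After dropout, 325 × 0.9 ≈ 292 are evaluable per arm, with power 79.8%. The design therefore has no slack after dropout.

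**Step 2: effect of a wait on a common 12-month clock.** Assumptions, none of them in the article: constant hazards; the 20% applies when the programme starts at randomisation; the control hazard applies during the wait; falls are counted for 12 months from randomisation in both arms.

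- Control hazard: −ln(0.70) = 0.357 per year.
- Intervention hazard: −ln(0.80) = 0.223 per year (ratio 0.626).
- With a mean wait of w weeks, the intervention proportion is P(w) = 1 − exp{−[0.357·w + 0.223·(52 − w)]/52}.

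| Mean wait | Intervention | Difference from 30% | Power, 292 per arm |
|---|---|---|---|
| 0 weeks | 20.0% | 10.0 points | 79.8% |
| 2 weeks | 20.4% | 9.6 points | 76% |
| 4 weeks | 20.8% | 9.2 points | 72% |
| 8 weeks | 21.6% | 8.4 points | 64% |

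**Step 3: what wait is plausible?** The article gives no recruitment rate. Suppose a group of g people fills at one centre that randomises r people a month, half of them to sLiFE. The mean wait is then [(g − 1)/2]/(r/2) months. For g of 12 to 14 and r = 24, 12, 8 or 4, this is about 0.5, 1, 1.5 or 3 months. If an assembled batch is allocated just before session 1, it is close to zero.

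**Step 4: effect under the visit timing in 3.8.** Suppose instead that falls are counted from baseline to the follow-up visit.

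- Control: 26 weeks at risk, 1 − exp(−0.357/2) = 16.3%.
- Intervention: w + 12 + 26 weeks at risk, 1 − exp{−[0.357·w + 0.223·38]/52}. This is 15.0% with no wait, 17.3% with 4 weeks and 19.6% with 8 weeks.

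The unequal time at risk exists even with no wait. A wait makes it worse and, on these assumptions, 4 weeks is enough to reverse the direction of the observed difference.

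**The case against.** The strongest reply is that the wait is inferred. The article does not say that a group must be full, or drawn from one centre, before it starts; it gives no interval between allocation and session 1; and it does not exclude batch allocation. Section 3.10 says that the first groups are still being gathered, which fits assembling people before allocating them. A journal article may also leave such detail to the full protocol. This stands, and it is why the point is conditional.

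Several stronger readings are tempting and are not supported:

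- **That the effect is diluted as a matter of fact.** Dilution on a common clock needs both a wait and fall counting from randomisation. Neither is stated. If falls were counted from session 1, the calculated power would stay at 79.8%.
- **That the sequence ignores centre, or uses simple randomisation and so misses the planned group sizes.** Section 3.5 gives only the ratio and the software. A list balanced within batches of 24–28 would give 12–14 per arm.
- **That people unable to attend come to light only after allocation, in one arm.** Section 3.2.2 already excludes, before allocation and in both arms, those unavailable for the intervention. A clash with a particular time slot could still appear later, but the exclusion covers much of this.

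What remains is that the order described puts allocation ahead of any group assembly, no rule links the two, and the different follow-up anchors in 3.8 are explicit.

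**Conclusion.** The point holds as a conditional one, and it is worth acting on because the remedy is cheap. As written, the order of steps allows intervention participants to wait at control-level risk, and 3.8 would add that wait to their follow-up alone. The article fixes neither the wait nor the start of fall counting, so the size is an assumed range: power of about 80% with no wait, falling to 76%, 72% and 64% for mean waits of 2, 4 and 8 weeks. That range rests on constant hazards, 30% against 20% over a common 12 months from randomisation, and 292 evaluable per arm. It is not a forecast for this trial, and the loss is nil if batches are already allocated just before session 1.

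**What to change.** In 3.5, state that consent and baseline tests are completed for an assembled batch at one health centre, about 24–28 people. Confirm availability for the planned slot as part of the existing exclusion in 3.2.2. Then allocate the whole batch 1:1, balanced within the batch, just before session 1. Start the fall logs and one follow-up clock for both arms on that day. Amend 3.8 so that both arms are timed from it, and bring the time points in 3.9 into line. Include centre in the falls model.

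If allocation in batches is already intended, a sentence in 3.5 settles the order; the common clock in 3.8 is still needed.

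The cost is a new allocation list and short wording changes; the sample size, programme content and outcomes stay as they are. The downsides are real: people in both arms wait between baseline and allocation, so baseline measurements are somewhat older, and finding a full batch who can attend one slot may make recruitment slower or more demanding.
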